## Abstract

**Background::**

Acupuncture therapy is frequently used to treat Knee Osteoarthritis (KOA) in clinic, and usually used local acupoints near the diseased knees as therapeutic targets. Some local acupoints appeared sensitization phenomenon which was called sensitized acupoints, which were regarded as important therapeutic targets to get better therapeutic effect on clinic. Therefore, it is necessary to explore the biological basis of acupoint sensitization. Meanwhile, there is a lack of an analysis of the metabolism for sensitized acupoints in KOA patients. Considering that acupuncture effect could be multi-targeted, omics (such as metabolomics) may be a useful method to reveal the relationship between sensitized acupoints and clinical efficacy of acupuncture.

**Methods and analysis::**

This study is a parallel design trial. Thirty KOA patients and 30 healthy volunteers will be recruited in this study. Mechanical pain threshold will be measured by Electron Von frey in order to confirm the highest sensitized acupoints. Then collect tissue fluid from the highest sensitized acupoints by micro dialysis technical, then apply electro-acupuncture method on the highest sensitized acupoints to treat KOA patients, after 20 sessions treatments, measure and collect again. Liquid chromatography-tandem mass spectrometry method will be used to analyze the metabonomics of dialysate.

**Results::**

This study will provide a high-quality evidence to reveal the local molecular mechanism of acupuncture sensitized acupoints for patient with KOA.

**Conclusion::**

This study will provide up-date evidence of whether acupuncture sensitized acupoints have local molecular mechanism for KOA.
Trial registration number: NCT03599180 (24 Jul. 2018)

## Introduction

1

Knee osteoarthritis (KOA) is a common type of arthritis seen in the middle-aged and elderly population^[1,2]^ which is accompanied with chronic pain, inflammation, and impaired motor function, leading to deterioration of quality of life.^[3]^ The main therapeutic goals in the treatment of osteoarthritis are pain relief and functional improvement.^[4]^ Related systematic review showed acupuncture is an effective therapy in treating KOA especially on the short-term pain relief and short and long-term physical function improve.^[5]^

Many studies chose acupoints around the knee joint to treat KOA.^[6–13]^ KOA has some clear pathological reaction points around the knee joint, even some of them overlap with acupoints.^[14–15]^ Some local acupoints appeared sensitization phenomenon, such as Zusanli (ST35), Yanglingquan(GB34), Sanyinjiao(SP6), and Dubi(ST35) were appeared heat-sensitized in KOA patients.^[16]^ Meanwhile, the improvement of joint pain, morning stiffness, joint swelling and walking ability after treatment at heat-sensitized acupoints with heat moxibustion method was much more apparent as compared with conventional moxibustion method.^[17]^ This sensitized phenomenon also existed in other diseases such as coronary artery disease,^[18]^ functional bowel disorders,^[19]^ cholecystitis,^[20]^ and it has been defined as acupoints sensitization which refers to the change of acupoints from silence to activation during pathological process.^[21]^

After acupoints sensitized, their physical properties may change, for instance, volt-ampere characteristics.^[22–24]^ And substances of acupoints may also change, such as ATP,^[25]^ adenosine,^[26]^ histamine (HA), serotonin (5-HT), calcitonin gene-related peptide (CGRP), substance P (SP), and TRPV-1 channel proteins.^[27–29]^ Those means the sensitized acupoints were caused by the change of a variety of substances or factors, not just one of the substances or factors. It is not known whether other substances work in sensitized acupoints. Most of these studies were conducted in animal models, it is necessary to conduct metabolomics studies in human body from a broad perspective on the matter of sensitized points, especially small molecules matter. Therefore, we designed this project to use micro dialysis, liquid chromatography-tandem mass spectrometry (LC-MS/MS) and high-throughput sequencing technology to analyze the non-targeted metabolomics, to screen out the key substances of sensitized acupoints.

## Methods

2

### Overview

2.1

This trial is a single-center, normal controlled, parallel group, clinical trial. The trial is an explorative, pilot trial designed to reveal the change of the main material group and key substances in sensitized acupoints caused by knee osteoarthritis.

The trial is being conducted at the affiliated hospital of Chengdu University of TCM, Acupuncture Outpatient Department, Si Chuan, and China. The trial was approved by the Chinese ethical committee on human research (reference NO. 2018KL-042), and this program is part of our clinical registration subject registered on www.clinical.trials.gov (reference NO. NCT03599180). The trial will be reported in compliance with the CONSORT statement (www.consort-statement.org).

### Sample size calculation

2.2

This study aims to investigate basic information about sensitized acupoints of KOA patients, rather than to satisfy hypothesis testing. Hence, the sample size was estimated by based on a rationale about feasibility, precision about the mean and variance, regulatory considerations and ethical issues that prohibit over-recruitment of participants. Considering an estimated 20% dropout rate, we assured that the sample size exceeded the minimal number needed to ensure the validity of the mean, effect size and rationale of feasibility. Therefore, a sample size of 60 participants was estimated.

### Recruitment KOA patient and healthy volunteers

2.3

A total of 30 KOA patients and 30 normal volunteers will be included, flow diagram in Figure 1. No interim analysis will take place. Subjects enrolled will have some financial compensation, and KOA patients can also receive 4 weeks free electro-acupuncture treatments. And all information about the subject will be kept strictly confidential until the end of the trial.

**Figure 1 F1:**
[figure not shown]
Illustrates the flow diagram of studies identified.

#### Diagnostic criteria of KOA patients

2.3.1

The criteria referenced the “*Osteoarthritis Diagnosis and Treatment Guideline*” (2018) formulated by Joint Surgery Group of Bone Science Branch of the Chinese Medical Association.I.Repeated knee pain occurred in the past month.II.X-ray imaging taken standing or weight-bearing, seen ipsilateral knee joint space narrowing, bone sclerosis or cystic changes with articular cartilage, knee edges seen with osteophyte formation.III.Patients age ≥50 years.IV.Morning stiffness is less than 30 minutes.V.Bone crepitus or bone friction feeling during activity.

Meet the diagnostic criteria I+ (any 2 of II, III, IV, V) can diagnose knee osteoarthritis.

#### KOA classification criterion

2.3.2

According to the imaging examination X-ray *Kellgren* and *Laerence* classification standards are as follows:I level: Knee joint space is suspiciously narrowed, possibly with the formation of osteophytes.II level: Knee joint space is suspiciously narrowed, visible osteophyte formationIII level: The narrowing of the joint space of the knee joint was relatively clear, showing that there was a moderate amount of osteophyte formation and may be accompanied by sclerotic changes.IV level: It can be seen that there are a large number of osteophyte formations, and the joint space of the knee joint is significantly narrowed and may be accompanied by sclerotic lesions and obvious joint deformities.

KOA patients in- and exclusion criteria are listed in Table 1.

**Table 1 T1:**
[figure not shown]
Inclusion and exclusion criteria of KOA patients.

#### Recruitment volunteers

2.3.3

Thirty healthy volunteers whose age over 45-year will be recruited in control group.

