### Intervention method

2.6

After highly sensitized acupoint screening and dialysate sample collecting, 5 to 6 sensitized acupoints will be chose to the main points. Then, KOA patients will receive electro-acupuncture treatment 5 sessions per week for 4 weeks, with continuous wave and durations of 30 minutes, the electricity intensity is based on the patient's tolerance. Relevant concomitant care and interventions that are permitted or prohibited during the trial. At the end of the treatment, the sensitized acupoints will be detected again to see whether MPTs had changed, and the previous most sensitized acupoint will be collected dialysate sample again.

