### Outcome measure

2.9

The primary outcome is the identified potential differences metabolites between KOA group and volunteer group will be the outcome measures. And the second outcome is the change of Western Ontarioand McMaster Universities Osteoarthritis Index (WOMAC) total score from baseline to 4 weeks of KOA patients.

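### The primary metabolite comparison is between unrandomised groups, and the only stated control rule (healthy, over 45) leaves age, sex and BMI free to confound it

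*Protocol article*

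**What the plan says.** All references are to the protocol article.

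- **Design (2.1, 2.3).** The Overview states: "This trial is a single-center, normal controlled, parallel group, clinical trial". Section 2.3 adds: "A total of 30 KOA patients and 30 normal volunteers will be included". Group membership is disease status. The Overview calls the trial an exploratory pilot, and gives its aim as finding the substances in sensitized acupoints whose change is due to KOA.
- **Primary outcome (2.9).** "The primary outcome is the identified potential differences metabolites between KOA group and volunteer group".
- **Controls (2.3.3).** The whole subsection is one sentence: "Thirty healthy volunteers whose age over 45-year will be recruited in control group".
- **Patients (2.3.1, 2.3.2).** Criterion III of the diagnosis is "Patients age ≥50 years". The rule for combining criteria is: "Meet the diagnostic criteria I+ (any 2 of II, III, IV, V) can diagnose knee osteoarthritis". Eligibility is in a table that is not reproduced: "KOA patients in- and exclusion criteria are listed in Table 1". Its caption also refers to KOA patients only.
- **Site (2.4, 2.5).** Volunteers are tested and sampled at the same acupoints as patients.
- **Analysis (2.7).** PCA and OPLS-DA are named.

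**The concern.** Without randomisation, the two groups are comparable only so far as the controls are chosen to be. The stated choice is health plus an age floor five years below the patients' age item, with no upper limit, no target age distribution and no balance on sex or BMI.

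The diagnostic rule favours older patients. Someone aged 50 or over with recurrent knee pain needs one more item from X-ray change, short morning stiffness and crepitus; someone younger needs two. A volunteer only has to be over 45.

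The assay is untargeted, so any small molecule that varies with age, sex or adiposity can appear as a group difference. The article intends to read such differences as substances linked to KOA and acupoint sensitization. A poorly chosen control group cannot be replaced once the microdialysis samples are taken, and adjustment afterwards works badly if 30 patients and 30 volunteers overlap little in age.

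**Working it through.** **The plan's own figure.** The total of 60 cannot be reproduced, because the article gives no alpha, power, effect size, SD or precision target. It does not need to be, since the number is not in dispute here. The stated 20% dropout, if it falls equally on both groups, leaves 30 × (1 − 0.20) = 24 evaluable per group.

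**Question.** How often would a metabolite that is unrelated to KOA but related to age be flagged?

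**Inputs**
- From the article: 30 per group (24 after dropout).
- Assumed, because the article gives none of them: age SD of 8 years; correlation r between metabolite and age; gap in mean age between groups; a two-sided t-test at 0.05 as a simple stand-in for the selection of differential metabolites.

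**Formulas**
- Spurious standardised difference: d = r × gap / 8.
- Noncentrality with n per group: d × √(n/2).
- Chance of p<0.05: noncentral t with 2n − 2 degrees of freedom.

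**The gap that the cut-offs alone would produce.** If ages were uniform on 45–75 in volunteers and 50–75 in patients, the means would be 60 and 62.5, a gap of 2.5 years. The SDs are 30/√12 = 8.66 and 25/√12 = 7.22, so the gap is 2.5/√((75 + 52.08)/2) = 0.31 SD. This is an illustration: 50 is not a strict floor for patients.

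**One case in full.** r = 0.3, gap 5 years, n = 30: d = 0.3 × 5/8 = 0.1875; noncentrality = 0.1875 × √15 = 0.726; chance = 11.0%.

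| Age gap (years) | d at r=0.3 | n=30, r=0.3 | n=24, r=0.3 | d at r=0.4 | n=30, r=0.4 | n=24, r=0.4 |
|---|---|---|---|---|---|---|
| 2.5 | 0.094 | 6.5% | 6.2% | 0.125 | 7.6% | 7.1% |
| 5 | 0.188 | 11.0% | 9.8% | 0.250 | 15.9% | 13.6% |
| 8 | 0.300 | 20.8% | 17.5% | 0.400 | 33.2% | 27.4% |
| 10 | 0.375 | 29.8% | 24.6% | 0.500 | 47.8% | 39.6% |

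At r = 0.1 and n = 30 the chance is 5.2% for a 2.5-year gap and 6.7% for 8 years, so weakly age-related metabolites are little affected. These are chances per metabolite. Sex and BMI are not quantified, because the article gives nothing from which their imbalance could be judged.

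**The case against.** The strongest reply is that the article condenses a fuller protocol, that patient eligibility sits in a table that is not reproduced, and that covariate adjustment can be left to a statistical analysis plan. The trial is an exploratory pilot whose sample size is expressly not built on hypothesis testing. Age 50 or over is one of four optional items, so younger patients can enter. If only the cut-offs differ, the inflation is slight.

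Much of this stands. It limits the point to a risk of unknown size, and it rules out saying that the results *will* be confounded. It does not remove the point. The control rule is stated, in a subsection of its own, and the missing table is described as covering patients. How controls are selected is a design feature, and later adjustment does not fully replace it. The exploratory label does not help either, since the primary outcome is still this contrast.

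Two stronger readings are tempting, and the article does not support them.

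- **Acupoint site as an uncontrolled confounder.** Sections 2.4 and 2.5 set the same acupoints for volunteers. What is unstated is only how one patient's most sensitized point is carried over to a volunteer.
- **Analgesics shown to enter the primary contrast.** The sentence in 2.6, "Relevant concomitant care and interventions that are permitted or prohibited during the trial", is unfinished and states no rule. However, it sits in the description of treatment, which starts after the first dialysate has been collected. Only patients are described as sampled again, so the comparison with volunteers most naturally uses that first sample. The sentence is a drafting fault, and does not show what medicines were taken before sampling.

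**Conclusion.** The point holds as a risk. As written, nothing in the article keeps the groups comparable on age, sex or BMI, so a metabolite that differs between them may reflect those factors and not KOA or sensitization.

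The age component is small if the groups differ only through their cut-offs, and material if they differ by about one SD: for r = 0.3 and 30 per group, from 6–7% to about 21% against a nominal 5%. These figures rest on the assumed SD, correlations and gaps, and on a test that the article does not name. They would fall away if the full protocol already matches volunteers to patients, in which case 2.3.3 should say so. The change is worth making before volunteers are recruited.

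**What to change.** **Recruitment (2.3.3).** Recruit volunteers frequency-matched to the enrolled patients on sex and age band, for example 5-year bands. With equal numbers in each band, the gap in mean age must stay below 5 years, and it will be near zero if ages are spread alike within bands. Allocate volunteers' sampling acupoints in the same proportions as the patients' most sensitized points.

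**Data and analysis.** Record BMI and current medicines in both groups before dialysis. Confirm each differential metabolite in a model adjusting for age, sex and BMI, and exclude drug-derived features. Complete the unfinished sentence in 2.6.

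**Cost.** Volunteer recruitment becomes somewhat slower, because it has to follow patient enrolment, at least in batches. The adjusted model uses three degrees of freedom: 58 become 55 with 60 participants, or 46 become 43 with 48. No extra participants or invasive procedures are needed.

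Individual 1:1 matching on several factors with within-pair analysis would be dearer. If dropout is independent at 20% in each group, only 30 × 0.8 × 0.8 = 19.2, about 19, complete pairs would remain. Frequency matching avoids that loss.

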### Mechanical pain threshold

2.4

Mechanical pain threshold (MPTs) test will be performed according to the recommendations of the German Research Network on Neuropathic Pain.^[30]^ Electronic Von frey will be used to contact the acupoints around the knee osteoarthritis joint and the same acupoints of volunteers. The final threshold was the geometric mean of three series of ascending and descending stimulus intensities.

Acupoints choose based from the analysis of the acupoints selection rules for randomized controlled trials of acupuncture for knee osteoarthritis in the modern literatures.^[31]^ And the point's locations are showed in Figure 2.

**Figure 2 F2:**
[figure not shown]
Illustrates these local points in knee osteoarthritis acupuncture therapy.

### Micro dialysis

2.5

The highest sensitized acupoint of KOA patients and the same acupoint of volunteers will choose for micro dialysis. Disinfect locally with 75% alcohol, cover disposable surgical hole towel. The skin overlying the muscle of the puncture sites will be anesthetized with a local injection (0.5 ml) of Lidocaine (Xylocaine 20 mg /ml), carefully avoiding anaesthetized the underlying muscle.

Insert introducer cannula into muscle tissue below acupoint. Guide the catheter (CMA 66 Liner Catheter, Membrane: PAES, Membrane length 10 mm, Cut-off 20,000 Dalton, Inlet 400 mm, Outlet 100 nm. M dialysis AB, Sweden) gently in to the sharp end of introducer cannula (Important: be very careful when entering membrane into introducer cannula). When catheter and membrane are in position, remove introducer cannula. Penetrate vial cap with a cannula (preferably 21G). Position cannula at the catheter outlet, removes the cannula from outlet, and then connect microvial. Then connect catheter to syringe filled with Perfusion Fluid (CMA, M dialysis AB, Sweden). Place the syringe in the microdialysis pump (CMA 106, M dialysis AB, Sweden). A 5 minutes flush will start indicated by a green signal every other second. Then after 120 minutes of equilibration the dialysate will collect every 60 minutes for a total of 3 collections. The dialysate will store frozen in –80° refrigerator as soon as possible.

### Intervention method

2.6

After highly sensitized acupoint screening and dialysate sample collecting, 5 to 6 sensitized acupoints will be chose to the main points. Then, KOA patients will receive electro-acupuncture treatment 5 sessions per week for 4 weeks, with continuous wave and durations of 30 minutes, the electricity intensity is based on the patient's tolerance. Relevant concomitant care and interventions that are permitted or prohibited during the trial. At the end of the treatment, the sensitized acupoints will be detected again to see whether MPTs had changed, and the previous most sensitized acupoint will be collected dialysate sample again.

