## Discussion

3

In this study we choose KOA as the vehicle for studying the phenomenon of acupoint sensitization. Because first, KOA has some clear pathological reaction points on the body surface often represented by changes in pain and thermo sensitivity.^[14]^ Secondly, KOA is the preponderant illness for acupuncture therapy.^[32]^

Von Frey monofilament is a classic pain measurement method in patients with allodynia and neuropathic pain.^[30,33]^ Clinical trials have shown that the Electronic Von Frey method is reliable for measuring MPTs. Electronic Von Frey measurement is based on an increasing stimulus intensity, Suzuki et al proved the electronic Von Frey device were significantly higher and more consistent than pinprick stimulators when tested MPTs in human.^[34,35]^

Micro dialysis is an in vivo sampling technique implant a probe into a dialysis site, such as brain tissue, muscle tissue, blood vessels, then to dialysis a biological sample.^[36]^ This method reflects real-time dynamic response to the components of tissue fluid and has been widely used in clinical practice since its beginning.^[37]^ Takahiro Takano applied micro dialysis technology to ST36 (Zusanli) Point to analyze the adenosine concentration of local tissue fluid after local acupuncture.^[38]^ In 2017, Swedish researchers placed micro dialysis probe into the masticatory muscles to analyze the changes of inflammatory molecular components in patients with masticatory cramps.^[39]^ The above studies found that the application of micro dialysis technology is mature and safe in clinical practice. In this study, we will use the micro dialysis device provide by CMA company. And the CMA 66 Liner Catheter has a semi permeable membrane with 20,000 Dalton molecular weight cutoff only small-molecular substances can pass through the membrane while micro molecular substances, such as proteins and cells are excluded.^[40]^ Considering the amount of substances exchange at micro liter level (0.3 μl/ minute), disruption of the fluid balance and the metabolic process could be neglected.^[41]^

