Studies have confirmed that acupuncture operations on sensitized acupoints can help to improve the clinical efficacy of acupuncture.^[16,17]^ We reckon that acupuncture may cause changes of small molecules substances in sensitized acupoints. These finding may also attribute to clinical appliance.^[14–16]^ Although there were studies reported that local mast cell degranulation might be the crucial progress to sensitization in the KOA animal model,^[48–51]^ it still remains unclear whether the rest of the substances are involved in this process and their role in acupuncture treatment process. Therefore, in this study, we will use LC-MS/MS to analyze the dialysate, and then apply non-targeted metabolomics strategy based on high-throughput method with huge data processing platform to describe the metabolic profiling of dialysate from sensitized acupoints of KOA patients. With these methods we hope to find other potential key substances of sensitized acupoints in KOA patients. This study may be able to provide a basis for understanding the systemic biological mechanisms of acupoints sensitization.

There are several limitations of this study. First, the sample size is small. But the results of this study may help us to know about some crucial information of sensitized acupoints in KOA patients. Other potential limitation of this study is the sensitization phenomenon has many types, such as pain-sensitized, heat-sensitized, morphologic change, and so on.^[21]^ We only study pain-sensitized phenomenon of KOA patient, the results of this study will be limited use in this disease to explain pain-sensitized.

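### If the pain-threshold screen that picks the sensitized acupoints is also the baseline for their change, a rise at those points is expected with no treatment effect

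*Protocol article*

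**What the plan says.** The Abstract of the protocol article gives the purpose of the threshold test: "Mechanical pain threshold will be measured by Electron Von frey in order to confirm the highest sensitized acupoints". The Discussion restricts the study to one kind of sensitization: "We only study pain-sensitized phenomenon of KOA patient". The most sensitized point is therefore naturally the one with the lowest threshold, although the article states no cut-off or formal definition.

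Section 2.6 (Intervention method) then uses the screen to choose the treated points: "5 to 6 sensitized acupoints will be chose to the main points". The single most sensitized point is used for microdialysis (section 2.5). After treatment, the Abstract says "after 20 sessions treatments, measure and collect again", and section 2.6 says "the sensitized acupoints will be detected again to see whether MPTs had changed".

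Only one pre-treatment MPT measurement is described. All KOA patients are treated. No untreated or sham KOA group is described, and no repeat MPT in the volunteers.

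MPT change is not among the outcomes in section 2.9, which names differential metabolites (primary) and change in WOMAC total score (secondary).

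**The concern.** A threshold reading contains the true sensitivity of the point and the error of that occasion. Points chosen because they read low are partly points whose error happened to be negative. On re-measurement that error is drawn afresh, so the average reading at the chosen points goes up without any change in the patient.

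This is the direction in which desensitization by electro-acupuncture would also move the reading. With one treated KOA group, the two cannot be told apart. Repeating the test in the volunteers would not settle it, because their point is taken over from the patients and not selected on their own low reading.

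At stake is any statement that treatment reduced sensitization at the selected points. Sensitization is the construct under study, so readers will give weight to such a statement even though it is not a named outcome.

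**Working it through.** The article states no figure for the MPT change, so there is nothing of its own to reproduce.

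**Inputs from the article**
- 30 KOA patients (section 2.3) and 20% dropout (section 2.2), so 30 × 0.8 = 24 completers.
- 5 to 6 points treated (section 2.6), one of them the most sensitized.
- Each reading averages three series (section 2.4): "The final threshold was the geometric mean of three series of ascending and descending stimulus intensities". This reduces error within a session, not from day to day.

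**Inputs assumed**
- Number of candidate points K. The text refers to a figure that is not shown ("And the point's locations are showed in Figure 2"). I take K = 8, with 6 and 15 as a range.
- Reliability r, the share of the variance between points within a patient that repeats on another occasion. The Discussion says only "Clinical trials have shown that the Electronic Von Frey method is reliable for measuring MPTs" and gives no value. I take 0.5, 0.7 and 0.9.
- Points have equal norms, errors are independent and normal on the log scale, and the treatment effect is zero.

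**Formula.** Scale the variance of a single reading across points within a patient to 1. The expected null rise is (1 − r) × |mean expected order statistic of the selected points|.

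For 8 standard normal values the six lowest expected order statistics are −1.424, −0.852, −0.473, −0.153, +0.153 and +0.473.
- Lowest point: 1.424.
- Mean of the 5 lowest: 2.749 / 5 = 0.550.
- Mean of the 6 lowest: 2.276 / 6 = 0.379.
- All 8: 0.

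Multiplying by 0.5, 0.3 and 0.1 gives the null rise. The last column is the share of 20,000 simulated null trials with n = 30 (n = 24 in brackets) in which a two-sided paired t-test at 5% would be significant, were one used.

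| Points compared (K = 8) | Null rise in SD, r = 0.5 / 0.7 / 0.9 | Falsely significant |
|---|---|---|
| Lowest | 0.71 / 0.43 / 0.14 | 98% / 86% / 40% (95% / 77% / 33%) |
| 5 lowest | 0.27 / 0.16 / 0.05 | 92% / 72% / 31% (85% / 62% / 26%) |
| 6 lowest | 0.19 / 0.11 / 0.04 | 71% / 49% / 20% (61% / 40% / 17%) |
| All 8 | 0 / 0 / 0 | about 5% |

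Shorter simulation runs differ from these percentages by a point or two.

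**Range over K.** With K = 15 the multipliers are 1.736 (lowest) and 1.032 (5 lowest), so the rise is 0.87 / 0.52 / 0.17 and 0.52 / 0.31 / 0.10. With K = 6 the 5 lowest give 0.253, so 0.13 / 0.08 / 0.03, and choosing 6 of 6 gives zero.

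**With an independent second baseline.** If the points are selected on reading 1 and change is taken from a separate reading 2, the simulated null rise is about 0 and the false-positive rate about 5%.

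**The case against.** The strongest reply is that the trial does not rest on this comparison. Section 2.1 calls it explorative and a pilot, section 2.2 disclaims hypothesis testing, and section 2.9 does not list MPT change. No test of MPT change is stated, so the false-positive rates belong to a test supplied here for illustration. This stands, and it limits the weight of the point. It does not remove it, because section 2.6 gives the repeat measurement an explicit purpose, and an exploratory aim excuses imprecision rather than a bias of known direction.

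The double use of the reading is also inferred. The article is condensed, and a separate baseline in the full protocol cannot be excluded. The wording of section 2.6 also leaves open whether the whole screen is repeated after treatment: it calls the resampled point the previous most sensitized one, which would make sense if a new screen might find another. If so, part of the fix is already in hand.

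Three stronger readings are tempting and not supported:
- A reader might infer that the trial will probably report a spurious treatment effect. The article announces no test, and at reliability 0.9 the illustrative error is 20% to 40%.
- A reader might apply the single-lowest-point figures to the quoted sentence. That sentence concerns the sensitized points in the plural, where with K = 8 the shift is roughly 2.5 to 4 times smaller.
- A reader might infer that a planned link between MPT change and metabolite change is biased. Section 2.7 lists PCA, OPLS-DA, metabolite identification and pathway analysis, and no such link.

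**Conclusion.** The point holds in conditional form. If the screening reading is the before value, which the text implies but does not state, a rise at the selected points is expected with no treatment effect, and nothing described in the design would reveal it. The direction is predictable unless readings are free of occasion error or all candidate points are selected.

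The size is uncertain, because both K and r are assumed. With 8 candidates and reliability 0.5 to 0.9 it is 0.71 to 0.14 SD for the single lowest point and 0.27 to 0.04 SD for the 5 or 6 selected points. These are SDs across points within a patient, not patient-level effect sizes.

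The primary metabolite comparison and the WOMAC change are not directly affected. This is a point to correct cheaply before data collection, not a flaw in the trial's named outcomes.

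**What to change.** State which reading is the baseline for MPT change and which points are re-measured. Then do one or both of the following:
- After selection and before treatment, take a second, independent MPT reading at the selected points and use it as their baseline.
- Re-measure every screened point at 4 weeks and report the change averaged over all of them beside the change at the selected points.

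Holding back one of the three baseline series as the before value is not enough, because all three share the error of that session. Suppose variances of 0.70 for true differences, 0.15 between sessions and 0.45 per series within a session. The full reading then has error 0.15 + 0.45/3 = 0.30 and a bias of 0.30 × 1.424 = 0.43 SD at the lowest of 8 points. Selecting on two series and using the third as baseline still leaves 0.15 × 1.424 / √(0.70 + 0.15 + 0.45/2) = 0.21 SD, and about 21% false positives. For the same reason the second reading should come from a separate session.

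Label the MPT change descriptive in either case. Natural history, placebo response and regression at patient level stay uncontrolled without an untreated KOA group.

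The cost is a few more minutes of von Frey testing, plus an extra session for the second reading if no existing visit can hold it. The average over all points dilutes a purely local effect, which is why it belongs beside the selected-point change. Neither change touches the treatment. Readings not taken at the time cannot be recovered later, so this should be settled before recruitment.
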